#### Missing Data

The *Study Limitations and Adaptations* subsection in the *Discussion* section discusses considerations regarding missing data on outcomes and covariates and their handling in the analyses.

### Ethical Considerations

The study protocol, informed consent forms, and procedures have been reviewed and approved by the Health Sciences South Carolina Institutional Review Board (the reviewing institutional review board [IRB]; Pro00120675) and the ethics review committee of the National Institute for Medical Research in Tanzania (NIMR/HQ/R.8a/Vol.IX/4242), as well as the relying IRBs at Duke University (Pro00111772), Emory University (STUDY00005518), and the University of North Carolina at Chapel Hill. Informed consent will be sought from all study participants.

To maintain confidentiality, interviewers will conduct the consent process in a private space or in a mutually agreed-upon location where other people are not present. The interviewers will read out the consent form to potential participants and answer any questions. The potential risks and benefits of participation as well as the details of data confidentiality and use will be carefully explained in culturally appropriate and understandable language. Participants can refuse to participate and will only be consented after the research staff is satisfied that they understand all substantive provisions of the informed consent document. Persons with obvious psychological or psychiatric disorders that preclude informed consent will be excluded. Participants will be asked to provide written consent. They will be provided with a copy of the consent form. Informed consent documents will be developed in English, translated into Kiswahili, and back-translated into English.

Participants in the trial will be aged ≥15 years and either pregnant in their last trimester of pregnancy or mothers or legal guardians of children aged 12 to 23 months. For adolescents aged 15 to 17 years who are pregnant or mothers of children aged 12 to 23 months and are otherwise eligible to participate in the study, we obtained a waiver of parental consent. Tanzanian national policy indicates that adolescents aged <18 years who are sexually active and pregnant have the right to access reproductive health services (eg, HIV testing, care, and treatment [31], as well as family planning [32]) without parental or spousal consent, and they can make associated medical decisions on their own behalf. Given that these adolescents have this *adult* right to medical decision-making, we posit that they are also able to consent to research participation for themselves without parental or spousal consent. Risks from participation in this study are considered commensurate with ordinary daily life.

Protocol amendments will be submitted to the relevant IRBs for approval before implementation. Adverse events will be reported to the ethics review committee of the National Institute for Medical Research in Tanzania and the US-based IRBs.

Participants will be compensated for the time they spend participating in study activities. Ethically and culturally appropriate compensation will be established in collaboration with community advisers and other key informants. Subject to IRB approval and discussions with key informants, incentive amounts may be adjusted during the study period to account for exchange rate fluctuations and cost-of-living increases.

## Results

Results are pending. The study was funded in August 2022. Data collection is expected to last from February 2024 to July 2027.

## Discussion

### Relevance

The Chanjo Kwa Wakati intervention and proposed evaluation are aligned with the strategic priorities of the Immunization Agenda 2030 and Tanzanian priorities for digital health and community health workforce development [33,34]. Specifically, our study builds on a Tanzanian digital health investment road map [35] to digitize health care data and is in line with Tanzania’s 2020 National Operational Guideline for Community-Based Health Care Services, which seeks to build a strong community health workforce for health promotion, including for child health [36]. The relevance of our study extends beyond rural Tanzania. The low-cost strategies developed and evaluated in this study are applicable to other rural contexts where some populations are less likely to be vaccinated, experience poor vaccine access, or express low confidence in vaccinations, and our study may inform the development and implementation of multipronged programs to promote timely vaccinations in such settings.

### Contributions to the Literature

Our study is expected to make several important contributions to the scientific literature on digital health and vaccination interventions. First, numerous studies have documented low timeliness of vaccinations for children from LMICs, with a disproportionate burden for rural children [4,6,37-41]. Our study is significant because it seeks to evaluate an intervention for promoting vaccination timeliness for rural children. Second, lay health care workers such as CHWs play a critical role in delivering health services in LMICs. Our study will use a hybrid digital and in-person approach and contribute evidence on effective and scalable strategies for supporting lay health workers with digital health tools to promote childhood vaccination equity. Third, although many studies have evaluated mobile phone–based reminders for promoting childhood vaccinations [10], evidence is lacking for community-based systems that target multifaceted barriers to vaccinations. Our study will contribute data on the effectiveness of a community-based digital health intervention to promote equitable and timely vaccination in LMICs. Fourth, research studies support the use of screening tools to identify vaccination knowledge gaps and deliver targeted interventions to combat vaccine hesitancy. Our study will integrate CHW outreach and mobile phone–based vaccination education to bridge gaps in vaccination knowledge, respond to parental concerns, and reduce hesitancy. Finally, our study will contribute evidence on strategies to bridge the *digital divide* in rural areas and the *gender gap* in mobile phone access by using a combined digital and in-person approach.

### Study Limitations and Adaptations

#### Unknown Number of Eligible Women per Cluster

Although we estimate that 20 clusters per region are required to reach our enrollment targets for the cross-sectional and longitudinal samples, neither the number of eligible women per cluster nor the number of refusals are known a priori. If the sample size across clusters is too small, sampling may be extended to additional clusters until sample size targets have been reached in each region and study arm.

#### Randomization

If the distributions of key characteristics of clusters vary greatly between the initially specified study arms (based on randomized IDs), a covariate-constrained randomization approach may be used that maximizes the balance across study arms in the distribution of key characteristics of clusters.

#### Spillover and Contamination

Cluster randomization is expected to minimize spillover effects; however, contamination may exist for participants living at the boundaries between intervention and nonintervention clusters. Sensitivity analyses will evaluate potential spillover effects by including geographic proximity to an intervention cluster as a covariate for the nonintervention group women in our models.

#### External Events

A potential threat to validity stems from the possibility of a local vaccination campaign or selective stockouts among subsets of clusters during follow-up. Given our collaboration with regional and national stakeholders, enrollment from multiple clusters, multiple vaccination time points for each participant, and the robust design, the likelihood and potential impact of such external events on our findings is low. The effects of stockouts on timeliness will be assessed in the *per-protocol* sensitivity analysis.

#### Missing Data

If vaccination cards are missing for >10% of the cross-sectional sample, and their vaccination information cannot readily be ascertained from records at the local health facility, enrollment into the cross-sectional cohort will continue until key outcome measures can be ascertained for the target number of 400 mothers. This may include the expansion of enrollment to additional clusters. Enrollment into the longitudinal cohort will be increased proportionately. Missing data on other characteristics will be addressed using full information maximum likelihood estimation or sensitivity analyses [42-45].

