### Study Setting

The study will be conducted in 4 rural districts in Mwanza and Shinyanga regions in Tanzania. Both regions have large numbers of unvaccinated or undervaccinated children. The populations of Mwanza and Shinyanga region were estimated to be 3,699,872 and 2,241,299, respectively [18]. In 2022, only 56% of children aged 12 to 23 months in Mwanza region and 32.2% of children in Shinyanga region were estimated to have received all basic vaccinations, including one dose of Bacillus Calmette-Guerin vaccine, 3 doses of polio vaccine, 3 doses of DPT-containing vaccine, and one dose of measles-containing vaccine [19]. Fewer children aged 12-23 month were considered fully vaccinated according to the national vaccination schedule shown in Table 1 (32.8% in Mwanza and 2.5% in Shinyanga) [19]. Notably, 3.3% of children aged 12-23 months in Mwanza and 14.5% in Shinyanga were reported to have received no vaccinations. [19].

**Table 1 table1:** Routine childhood immunizations recommended in Tanzania before age 1 year.

Antigen	Age at vax due date
Bacillus Calmette-Guerin (BCG) and oral polio vaccine (OPV) 0	At birth or first contact
OPV1; pentavalent vaccine comprising antigens of diphtheria, pertussis, tetanus, *Hemophilus influenza* B, and hepatitis B (Penta) 1; pneumococcal vaccine (PCV) 1; and rotavirus vaccine (Rota) 1	6 weeks
OPV2, Penta2, PCV2, and Rota2	10 weeks
OPV3, Penta3, PCV3, and injectable polio vaccine (IPV)	14 weeks
Measles and rubella 1	9 months

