### Study Design

#### Cluster Randomized Trial Design

Forty rural health facilities and their catchment areas (*clusters*), 20 per region, will be randomized to an (A) early or (B) delayed onset study arm (Figure 2). From each cluster, 3 cohorts of 10 mother-child dyads (1 retrospective cohort and 2 prospective cohorts) will be enrolled into the study. For the retrospective cohort, 400 mothers of children aged 12 to 23 months (10/cluster) will be enrolled as a cross-sectional sample for retrospective assessments of children’s vaccination records during the first year of life. These cohorts, denoted by A1 and B1, will be part of the care-as-usual control group. For the longitudinal prospective cohort, 800 pregnant women in their last trimester of pregnancy will be enrolled during 2 rounds of enrollment (10 women/enrollment round/cluster) for prospective assessments of their children’s vaccination records during the first year of life. These cohorts are denoted by A2, A3, B2, and B3. In the first round of enrollment, 200 (50%) of the 400 prospective participants (those enrolled from early onset clusters; A2) will receive the intervention, and the other 200 (50%) participants (B2) will be part of the care-as-usual control group. In the second round of enrollment, all 400 participants (A3 and B3) will receive the intervention. In total, vaccination uptake and timeliness will be observed for 1200 children (n=600, 50% intervention group children and n=600, 50% nonintervention group children) during their first year of life. The nonintervention group children represent the *care-as-usual* control group in the trial.

The trial design, which analytically resembles a difference-in-difference design, allows for an analysis of the effectiveness of the intervention even in the context of contemporaneous changes in the rate and timeliness of vaccinations at the national level (eg, through national vaccination campaigns or changes in the vaccination schedule).

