### Outcomes Assessments

Vaccination outcomes are described in Table 3. Vaccination coverage and dates will be ascertained for each study child using government-issued vaccination cards, which will be photographed, scanned, or copied and entered by research staff. For the retrospective cohort, the enrollment survey will assess vaccination outcomes for the child; their participation will end after the enrollment survey. Outcome data for the prospective cohort will be collected during an endline survey 12 to 15 months after the birth of the child. All vaccination doses of all vaccination series will be tracked. For women who cannot provide vaccination cards at the time of the survey, consent will be sought to access their children’s paper-based or electronic vaccination records at their local health facility.

**Table 3 table3:** Outcome measures for the cluster randomized controlled trial.

Outcome measure	Type	Source
Timeliness of the third dose of the pentavalent vaccine, Penta3 (number of days delayed)	Primary	Vaccination cards
Timeliness of Penta3 (≤28 days delayed)	Secondary	Vaccination cards
Timeliness of all other vaccine doses recommended by age 1 y (number of days delayed)	Other	Vaccination cards
Coverage of all vaccine doses recommended by age 1 y	Other	Vaccination cards

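### Filling the retrospective control cohort by whether outcomes can be ascertained can leave never-vaccinated children out of two thirds of the controls

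*Protocol article*

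**What the plan says.** The rule is in the protocol article's Discussion, under Study Limitations and Adaptations, Missing Data. Its condition reads "If vaccination cards are missing for >10% of the cross-sectional sample, and their vaccination information cannot readily be ascertained from records at the local health" (the sentence goes on to name the facility). When the condition is met, "enrollment into the cross-sectional cohort will continue until key outcome measures can be ascertained for the target number of 400 mothers". For the prospective children the text adds only "Enrollment into the longitudinal cohort will be increased proportionately". The statistical methods named there for missing data apply to characteristics other than these outcomes.

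Under Cluster Randomized Trial Design, the retrospective cohorts are controls: "These cohorts, denoted by A1 and B1, will be part of the care-as-usual control group". The remaining controls are prospective: "the other 200 (50%) participants (B2) will be part of the care-as-usual control group".

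Outcomes Assessments names the source: "Vaccination coverage and dates will be ascertained for each study child using government-issued vaccination cards". The fallback, for any cohort, is the child's record at the local facility.

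The Quantitative Analysis of Intervention Effectiveness section compares mean outcomes between all intervention and all nonintervention participants and describes the result as unbiased because of randomization. It then adds accelerated failure time (AFT) models.

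**The concern.** A child who never attended for vaccination is the one most likely to have neither card nor facility record. If 400 places are filled by children whose outcome is documented, A1 and B1 are partly selected on vaccination contact, which is close to selecting on the outcome.

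The prospective cohorts are formed differently. Women enter in the last trimester, before any vaccination contact. The Retention section gives them extensive contact tracing and, on relocation or travel, proxy reports. For intervention children, Table 2 has community health workers register the birth and check vaccination status after each due date. Loss of undocumented, never-vaccinated children is therefore likely to be smaller there. Enlarging the prospective cohort in proportion restores numbers; it does not make the cohorts comparable.

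At stake is the pooled contrast. Controls could look better vaccinated and more timely than they are, so that part of a real benefit is hidden.

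**Working it through.** **Plan's own figures.** Retrospective: 40 clusters × 10 = 400. Prospective controls (B2): 200. Total controls: 400 + 200 = 600, as stated ("n=600, 50% intervention group children and n=600, 50% nonintervention group children"). Share of controls under the rule: 400/600 = 66.7%. No intervention child is under it.

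**Never-vaccinated share.** Study Setting gives "3.3% of children aged 12-23 months in Mwanza and 14.5% in Shinyanga were reported to have received no vaccinations". Each region supplies 20 clusters of equal target size, so the simple mean fits the sample: (3.3 + 14.5)/2 = 8.9%.

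**Does that share trip the trigger?** The trigger is defined on the whole cross-sectional sample, and 10% of 400 is 40 children. Never-vaccinated children number 0.089 × 400 ≈ 36 if all lack cards and about 18 if half do. Neither exceeds 40, so some cards must also be missing among vaccinated children.

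**Coverage illustration.** Assumptions not in the protocol: true Penta3 coverage of 70%; trigger met; a fraction f of never-vaccinated children left out of A1/B1; no comparable loss in the prospective cohorts; left-out children have no Penta3.

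Retrospective coverage = 0.70 / (1 − 0.089f); pooled control shift = 2/3 of the retrospective shift.

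| f | Retrospective coverage | Shift in A1/B1 | Shift in pooled controls |
|---|---|---|---|
| 0.5 | 0.70/0.9555 = 73.3% | +3.3 points | +2.2 points |
| 1 | 0.70/0.911 = 76.8% | +6.8 points | +4.6 points |

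**If prospective cohorts also lose a fraction g.** Before any effect, the spurious difference is 2/3 × [shift(f) − shift(g)].
- f = 1, g = 0.5: 2/3 × (6.84 − 3.26) = 2.4 points.
- f = 0.5, g = 0.25: shift(0.25) = 0.70/0.97775 − 0.70 = 1.59 points, so 2/3 × (3.26 − 1.59) = 1.1 points.
- f = g: zero.

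**Binary timeliness.** Assume 52.2% timely among all children (100 minus the 47.8% rural delay in the Background). Pooled control timeliness rises by 2/3 × (0.522/0.9555 − 0.522) = 1.6 points at f = 0.5 and 2/3 × (0.522/0.911 − 0.522) = 3.4 points at f = 1, with g = 0.

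**Delay, with unvaccinated children kept at a cap.** Take age 365 days as the end point, so the cap is 365 − 98 = 267 days, and assume a mean delay of 28 days in other children.
- True mean: 0.089 × 267 + 0.911 × 28 = 49.3 days.
- At f = 0.5 the never-vaccinated share in A1/B1 is 0.0445/0.9555 = 4.66%, giving a mean of 39.1 days.
- Pooled control mean: (400 × 39.1 + 200 × 49.3)/600 = 42.5 days, about 6.8 days too low.

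With 14 to 56 days assumed for other children, the shift is 6.0 to 7.2 days. At Mwanza's 3.3% with a quarter left out it is 1.1 to 1.4 days. This capped mean is not the AFT estimate. It also should not be set against the protocol's 7-day target and SD of 28 days: the split between never-vaccinated and other children alone gives an SD of √(0.089 × 0.911) × 239 ≈ 68 days.

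**The case against.** The strongest reply is that the rule adds children and nowhere says that undocumented ones are dropped; their handling could sit in an analysis plan that is not shown. That is fair as to wording. But a target defined by ascertained outcomes places undocumented children outside the 400, and for missing outcomes the article offers no other remedy.

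Second, all cohorts use the same sources, and the prospective cohort grows in proportion. If 20% were unascertainable everywhere, 400/0.8 = 500 and 800/0.8 = 1,000 would be enrolled, with the same selection in each and no bias in the contrast. This stands as a limit: the bias needs unequal loss. The earlier enrollment, tracing and health-worker checks make unequal loss plausible, but the protocol gives no figure.

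Third, a mean delay among vaccinated children only gives a never-vaccinated child no value in any cohort. That also stands. The bias acts on the AFT model, binary timeliness and coverage.

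A reader might go further on three counts that the documents do not support.
- Zero-dose children are not removed outright. In the Background the term means no first DPT-containing dose, and a child with only birth doses on a card is ascertainable and stays.
- It is not established that the prospective cohorts lose none of these children.
- Shinyanga's 14.5% does not by itself trip the trigger, which applies to the pooled sample.

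**Conclusion.** The concern holds in conditional form. If the trigger is met, the rule can leave never-vaccinated children with neither card nor record out of two thirds of the controls, probably more often than such children are lost from the prospective cohorts. The pooled comparison is then not unbiased as claimed; the bias runs toward the null.

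On coverage the illustration gives about 2.2 to 4.6 points when half to all of these children are left out. It shrinks to 1.1 to 2.4 points if the prospective cohorts lose half as large a fraction, and vanishes if losses are equal. All of this rests on the assumed 70% coverage, the 8.9% share and assumed fractions undocumented; none is a protocol estimate of bias.

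The rule does not touch the concurrent A2 versus B2 contrast. Because it affects A1 and B1 alike, an analysis with phase effects would remove most of the bias, but the pooled comparison as written has none. This is a worthwhile and inexpensive improvement, not a fatal flaw.

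**What to change.** - Keep every enrolled retrospective child in the analysis denominator. Do not fill the 400 by ascertainability. Extra enrollment to protect precision is harmless if the undocumented children already enrolled stay in.
- Class a child with no card, no facility record and a caregiver report of no vaccination as unvaccinated: not covered, not timely, and censored in the AFT model.
- Treat other undocumented children as having a missing outcome, with a sensitivity analysis.
- Apply the same rule to all cohorts, and report ascertainment by cohort and arm.

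The cost is one reworded rule and one caregiver question, and it is lowest before retrospective enrollment starts. The downside is reliance on a caregiver's report of no vaccination for a minority of children, in a trial whose outcomes otherwise rest on documents.

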#### Mobile Phone Access and Use

In the target population, mobile phone access and use is not universal, and mobile phones may be shared within households. Chanjo Kwa Wakati is specifically designed to compensate for gaps in mobile phone ownership and coverage, including through the designation of vaccine advocates who will receive reminders and in-person outreach by CHWs to those who are not reached by mobile phone.

#### Sustainability of Reminders and Incentives

Reminder messages and incentive offers, which were informed by our prior work, will be carefully reviewed by investigators and key informants to ensure their ethical implementation and sustainability for a scaled-up intervention.

#### Generalizability

To assess the generalizability of the study’s context and findings, study data and the relationships among key variables of interest will be compared with information in publicly available survey data and administrative data sources.

### Interpretation and Dissemination

If successful, this study will contribute data on the effectiveness and implementation of the Chanjo Kwa Wakati intervention that engages recent mothers to increase the timeliness and coverage of routine childhood vaccinations in rural Tanzania. Key findings will be presented in peer-reviewed manuscripts, presentations at national and international conferences, and media outlets. Policy and programmatic recommendations will be developed in collaboration with key informants and decision makers at the national, regional, and district levels.

